# Efficacy of thunder-fire moxibustion for cancer-related fatigue in breast cancer survivors: study protocol for a randomized controlled trial

**DOI:** 10.3389/fonc.2025.1496741

**Published:** 2025-03-11

**Keywords:** moxibustion, cancer-related fatigue, breast cancer, randomized controlled trial, clinical trial protocol

## Abstract

**Background:**

Cancer-related fatigue (CRF) is one of the most prevalent and debilitating symptoms experienced by breast cancer survivors, often associated with dysregulation of the hypothalamic-pituitary-adrenal (HPA) axis. In China, moxibustion is widely used as a therapeutic approach for managing fatigue. Thunder-fire moxibustion (TFM), a novel technique with high thermal radiation and strong penetrative properties, may provide benefits for CRF. This study aims to assess the efficacy, safety, and underlying mechanisms of TFM in the treatment of CRF among breast cancer survivors.

**Methods:**

This prospective, single-center, open-label, randomized controlled trial will recruit 70 breast cancer survivors diagnosed with CRF. Participants will be randomly assigned in a 1:1 ratio to either a waitlist control group or a TFM intervention group. All participants will receive standard care during the 30-day treatment period. Those in the TFM group will additionally undergo TFM treatment every other day, totaling 15 sessions. The primary outcome measure is the change in total fatigue score, assessed using the Piper Fatigue Scale, from baseline to the end of treatment. Additionally, this study will investigate the underlying mechanisms of TFM by evaluating changes in HPA axis-related hormone levels, inflammatory markers, gut microbiota composition, and conducting metabolomic analyses of fecal and blood samples.

**Discussion:**

This study takes a multidisciplinary approach to comprehensively explore how TFM modulates biological systems involved in CRF, aiming to generate robust evidence. If successful, this study will provide high-quality, evidence-based reference points for the treatment of CRF in breast cancer survivors and inform future research in integrative medicine.

**Trial registration:**

The study has been registered with the International Traditional Medicine Clinical Trial Registry (http://itmctr.ccebtcm.org.cn, ITMCTR2024000406).

## Introduction

1

The National Comprehensive Cancer Network defined cancer-related fatigue (CRF) as “a distressing, persistent, subjective sense of physical, emotional, and/or cognitive tiredness or exhaustion related to cancer or cancer treatment that is not proportional to recent activity and interferes with functioning” (1). Recognized as one of the most common and burdensome symptoms, CRF affects over half of all cancer patients (2). According to the latest data from GLOBOCAN 2020, breast cancer, with an estimated 2.3 million new cases, has overtaken lung cancer as the most frequently diagnosed cancer worldwide (3). Notably, CRF is more prevalent among patients with breast cancer, showing a higher incidence rate than in other cancer types (4). Over 90% of breast cancer patients experience CRF during or after treatment (5, 6), and approximately one-third of these patients suffer from moderate to severe levels of CRF (7). Current treatment options for CRF include primarily pharmacological and non-pharmacological schemes (8). Non-pharmacological treatments, including exercise, psychological support, cognitive-behavioral therapy, and sleep management, are the mainstay, yet their efficacy is often limited. Pharmacological treatments typically involve stimulants and corticosteroids, yet their use is often limited due to associated side effects. Consequently, the imperative to explore and implement new strategies to alleviate CRF in breast cancer patients, with the goal of improving their quality of life, has become a critical area of concern.

Moxibustion, a revered external treatment modality in traditional Chinese medicine, boasts a history exceeding 2,500 years (9). This technique, which entails burning moxa to stimulate specific acupuncture points, is widely employed across Asia for symptom management in cancer patients (10). According to the principles outlined in the classic Chinese medical text “The Inner Canon of the Emperor”, the theory of “warming the deficient” suggests that conditions characterized by deficiencies in yin and yang, such as CRF, should be treated with warmth. Moxibustion, based on the theory of meridians, aims to enhance the circulation within the meridian system, thereby warming and supplementing the vital energy (qi) and balancing yin and yang (11). Throughout ancient Chinese medical literature, it has been extensively documented as an effective method for treating fatigue. Recent meta-analyses further support its benefits in alleviating CRF symptoms (12, 13). Among the various moxibustion techniques, the most widely applied in current CRF research is traditional mild moxibustion. Other notable methods include governor vessel moxibustion and laser moxibustion. Governor vessel moxibustion offers the advantage of stronger thermal radiation, greater penetration, and broader coverage compared to mild moxibustion (14). However, it is more complex to perform, requiring multiple auxiliary tools and is associated with higher costs. In contrast, laser moxibustion mimics the heat radiation effect of moxibustion, offering precise, stable, and adjustable thermal radiation (15). However, it is important to note that traditional moxibustion’s combustion effects may involve multiple pathways, such as aromatic and herbal components (16).

Thunder-fire moxibustion (TFM), an innovative moxibustion therapy, was developed by [name], drawing from her extensive medical experience spanning several decades (17). Currently, TFM is widely applied for musculoskeletal, respiratory, and neurological disorders (18). Preliminary meta-analytic evidence supports its efficacy in conditions such as back pain (19), knee osteoarthritis (20), allergic rhinitis (21), and postherpetic neuralgia (22). TFM, similar to governor vessel moxibustion, demonstrates high thermal radiation, deep penetration, and broad coverage (23). However, it offers superior cost-effectiveness, a simplified procedure, and eliminates the need for auxiliary tools. Compared to laser moxibustion, TFM does not require specialized equipment, making it more accessible and potentially effective through multiple mechanisms. Given the existing body of moxibustion research and the unique advantages of TFM, we hypothesize that TFM may prove to be an effective, economical, and accessible treatment for CRF.

To preliminarily explore the efficacy of TFM, we conducted a pilot study on breast cancer survivors who had completed cancer treatment and were in long-term follow-up. The selection of this specific cohort was based on practical feasibility. If CRF patients undergoing cancer treatment were chosen, perfect coordination with oncologists would be necessary, introducing complexity and additional confounding factors to the trial. Furthermore, considering the potential for cancer treatments to cause adverse events (AEs) and TFM’s potential to worsen these effects, this therapy was cautiously introduced only after fully establishing the safety of TFM. In this pilot study, 30 breast cancer survivors suffering from CRF randomly assigned to a moxibustion group (standard care + TFM every other day) and a control group (standard care). At the end of the 30-day treatment period, the total fatigue scores on the Piper Fatigue Scale (PFS) for the moxibustion group and the control group decreased by 1.93 points and 0.94 points, respectively, compared to baseline. No dropouts or treatment-related adverse events occurred in either group. Based on the feasibility and safety demonstrated by the pilot study results, the current study is designed to conduct a comprehensive randomized controlled trial to delve deeper into the therapeutic efficacy and safety profile of TFM for this patient demographic. Additionally, this study will explore the mechanism of action of TFM by analyzing changes in hypothalamic-pituitary-adrenal (HPA) axis-related hormone factors, inflammatory markers, gut microbiota, and conducting metabolomic analyses of fecal/blood samples.

## Methods

2

### Study design

2.1

The study is designed as a prospective, single-center, open-label, parallel-group, randomized controlled clinical trial. It aims to evaluate the efficacy and safety of TFM treatment in breast cancer survivors with CRF and to preliminarily explore its potential mechanisms. The study duration is 65 days, including a 5-day screening period, a 30-day treatment period, and a 30-day follow-up period. We plan to enroll 70 participants at the Hospital of Chengdu University of Traditional Chinese Medicine, who will be randomly assigned in a 1:1 ratio to either the waitlist control (WC) group or the TFM group. During the 30-day treatment period, all patients will receive standard care. Patients in the TFM group will receive additional TFM treatment every other day, for a total of 15 sessions. The primary outcome measure is the change in the total fatigue score on the PFS at the end of treatment compared to baseline. The study flow is illustrated in **Figure 1**.

**Figure 1 f1:**
[figure not shown]
Study flow diagram. HPA, hypothalamic-pituitary-adrenal; TFM, thunder-fire moxibustion; WC, waitlist control. Serum HPA axis-related hormones include adrenocorticotropic hormone, corticotropin-releasing hormone, and cortisol. Serum inflammatory markers include interleukin-6 and interleukin-8.

### Participants

2.2

#### Recruitment

2.2.1

Participants will be recruited through the posting of flyers on the bulletin boards at the Hospital of Chengdu University of Traditional Chinese Medicine, as well as through social media outreach (hospital website, WeChat, Weibo). Eligibility for the study will be jointly determined by a licensed oncologist and an acupuncturist, based on inclusion and exclusion criteria. Researchers will inform potential participants about the purpose of the study, its requirements, the interventions involved, and all potential risks, ensuring that they fully understand the study parameters before providing their signed informed consent.

#### Inclusion criteria

2.2.2

(1) Meets the International Classification of Diseases, 10th Revision (ICD-10), diagnostic criteria for CRF;(2) Moderate to severe fatigue, defined as a score of ≥4 on the PFS;(3) Diagnosed with stage I-III breast cancer in women;(4) Age between 18 and 80 years old;(5) Karnofsky Performance Status (KPS) score of ≥70;(6) Completion of breast cancer treatment (surgery, radiotherapy, chemotherapy, targeted therapy) at least 12 weeks prior, but ongoing endocrine therapy exceeding 4 weeks is allowed.

#### Exclusion criteria

2.2.3

(1) Pregnancy or breastfeeding;(2) Anemia (hemoglobin < 110g/L);(3) Abnormal thyroid function tests (free thyroxine > 22pmol/L, thyroid-stimulating hormone > 5.0uIU/ml);(4) Abnormal liver function tests (elevated aspartate aminotransferase or alanine aminotransferase levels greater than twice the upper limit of normal, or bilirubin levels exceeding the upper limit of normal, including total, direct, or indirect bilirubin);(5) Abnormal renal function tests (creatinine more than 1.5 times the upper limit of normal);(6) Patients with psychiatric disorders (including but not limited to depression, schizophrenia, bipolar disorder) or severe cognitive impairment (e.g., significant difficulties with memory, attention, or executive functions) that affect the ability to fully understand the study content or comply with the study protocol.

#### Drop-out criteria

2.2.4

(1) Participants have the right to voluntarily withdraw from the trial at any stage for any reason;(2) Participants who do not formally declare their withdrawal but independently cease the prescribed treatment or participation in related examinations, or cannot be contacted during the follow-up period, will be considered to have substantively withdrawn from the trial;(3) Participants who experience severe AEs that preclude continuation in the trial;(4) Participants who show poor compliance, with fewer than 12 TFM sessions;(5) Participants who use CRF treatments outside the study protocol (e.g., stimulants or corticosteroids).

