### Interventions

2.3

All patients will receive the standard care for CRF as recommended by the Oncology Branch of the Chinese Medical Association (24). The specific regimen will include: 1) Psychological support: imparting knowledge on breast cancer recovery and CRF, and engaging in weekly therapeutic communication with the patients, each session lasting approximately 2 hours, to assist in managing adverse emotions; 2) Nutritional management: conducting a nutritional risk assessment once a week using the Nutritional Risk Screening 2002 (NRS 2002) tool, with patients identified at nutritional risk being referred to the nutritional department for specialized treatment; 3) Sleep management: overseeing the establishment and maintenance of regular sleeping schedules and environments conducive to sleep, with pharmacological treatment being administered as necessary; 4) Exercise guidance: supervising patients to partake in 180 to 300 minutes of moderate-intensity physical activities per week, such as brisk walking, yoga, and Tai Chi. During the study, the use of treatments outside the study protocol for CRF will be prohibited (e.g., stimulants or corticosteroids).

The TFM group will receive TFM therapy. The moxa sticks used for the treatment are produced by Chongqing Zhao’s Thunder-Fire Moxibustion Traditional Medicine Research Institute in China, each measuring 2.8 cm in diameter, 10.5 cm in length, and weighing 230 g. TFM will be carried out by four female acupuncturists, each with more than three years of experience in moxibustion therapy and holding a professional license. The acupoints for treatment will include CV6 (Qihai), CV4 (Guanyuan), SP6 (Sanyinjiao), and both sides ST36 (Zusanli). The acupuncturists will manipulate a lit moxa stick, moving it up and down at a vertical distance of 2-3cm from the skin over the acupoints for 30 minutes, inducing a sensation of deep tissue warmth without causing any burn pain. The treatment frequency will be every other day for 30 days, totaling 15 sessions. The WC group is scheduled to commence TFM therapy following the conclusion of the study.

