### Statistical analysis

2.9

All analyses will be conducted within the intention-to-treat population, encompassing all randomized participants. For continuous variables, data adhering to a normal distribution will be expressed as mean ± standard deviation, while non-normally distributed data will be presented using the median and interquartile range. The Shapiro-Wilk test will be used to determine the normality of the data. Categorical variables will be depicted as frequencies and percentages. The planned statistical analyses will be conducted using SPSS software (version 28.0) and the R programming language (version 4.3.1). Significance testing will be bilateral, with a P-value of ≤ 0.05 denoting statistical significance.

To compare the longitudinal trajectories of changes in PFS scores from baseline between groups at successive follow-up time points, linear mixed models will be employed. Given the correlation between repeated measures within the same participant, this model will include participant-specific random effects (29). The fixed effects of the model will include group, follow-up time, and the interaction between group and follow-up time (30). Covariates will include age and baseline PFS scores. No imputation of missing data is planned, as the analysis model itself accounts for missing data and remains valid under the missing-at-random assumption.

For other continuous outcome measures, such as KPS scores, HPA axis-related hormonal factors, and inflammatory markers, comparison between groups will employ analysis of covariance adjusting for baseline values if the data are normally distributed. If not, the Mann-Whitney U test will be applied. Missing data will be addressed through the application of the last observation carried forward method.

We plan to conduct predefined subgroup analyses for the primary outcome, considering the following baseline variables: age (≤55, >55), nutritional risk (no, yes), sleep disorder (no, yes), fatigue severity (moderate, severe), body mass index (≤24, >24), KPS score (70, 80, 90, 100), cancer stage (I, II, III), cancer subtype (Luminal A, Luminal B, HER2-positive, triple-negative), and cancer treatment (surgery, radiotherapy, chemotherapy, targeted therapy, endocrine therapy). Consequently, except for the primary outcome, the interpretations of other outcomes and subgroup analyses will be treated as exploratory.

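### The drop-out criteria merge non-adherence and use of other fatigue treatment with leaving the trial, and the protocol does not say that these patients stay in PFS follow-up for the intention-to-treat analysis

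*Protocol article*

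**What the plan says.** The protocol article, section 2.2.4 (Drop-out criteria), has five entries. Three matter here.

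- Criterion 2, on leaving the study without a formal withdrawal, concerns patients who "independently cease the prescribed treatment or participation in related examinations, or cannot be contacted during the follow-up period, will be considered to have substantively withdrawn".
- Criterion 4: "Participants who show poor compliance, with fewer than 12 TFM sessions". Section 2.3 plans 15 sessions ("The treatment frequency will be every other day for 30 days, totaling 15 sessions"), so four missed sessions trigger it.
- Criterion 5: "Participants who use CRF treatments outside the study protocol (e.g., stimulants or corticosteroids").

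Section 2.9 (Statistical analysis) then states: "All analyses will be conducted within the intention-to-treat population, encompassing all randomized participants". For the PFS mixed model, "The fixed effects of the model will include group, follow-up time, and the interaction between group and follow-up time", with age and baseline PFS as covariates. On missing PFS scores: "No imputation of missing data is planned, as the analysis model itself accounts for missing data and remains valid under the missing-at-random assumption".

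Section 2.4.1 schedules the PFS at baseline and on days 10, 20, 30 and 60; the day-30 change is primary. Section 2.7 inflates the sample size for 20% dropout. No section says whether patients who meet criteria 2, 4 or 5 are still assessed.

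**The concern.** An intention-to-treat analysis needs outcomes from patients who stopped or strayed from treatment, not only a rule that keeps their names in the denominator. Section 2.2.4 gives such patients the same status as patients who leave the study. If sites follow it literally, visits stop and day-30 scores are never taken. An analysis plan cannot recover them later.

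The rules are also not neutral between the arms. Only TFM patients can meet criterion 4, because the waitlist arm has no sessions to miss. Criterion 5 can be met in either arm. Both concern events that plausibly relate to fatigue: a patient who feels no benefit may stop attending, and one who feels worse may seek other help. The trial is open-label and its primary outcome is patient-reported, so this is a realistic route.

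What is at stake is the meaning of the primary estimate: the effect of being assigned to TFM, or the effect had everyone kept to it.

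**Working it through.** **1. What the plan's own sample size implies about drop-outs.** Inputs from section 2.7: changes of 1.93 (SD 0.47) and 0.94 (SD 0.35), margin 0.5, one-sided α 0.025, power 0.99, dropout 20%.

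- Net difference: 1.93 − 0.94 − 0.5 = 0.49. Variance sum: 0.47² + 0.35² = 0.3434.
- Unequal-variance t-test: 27 per arm gives power 0.9892, and 28 gives 0.9913, so 28 are needed.
- Inflation: 28 / (1 − 0.20) = 35. The stated figure reproduces exactly.

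Dividing by 0.8 counts drop-outs as giving no primary-outcome data. That fits the reading that their scores are lost, but does not prove it.

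**2. When criterion 4 can take effect.** If the first session is on day 1, the fourth falls on day 1 + 3 × 2 = 7, and the fifteenth on day 1 + 14 × 2 = 29. A patient can therefore meet the rule before the first post-baseline PFS, between visits, or just before day 30. Applied as soon as it is met, it can cost the day-30 score. Applied only at the end of treatment, it either has no effect or would set aside scores already taken, which section 2.9 does not allow.

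**3. What the mixed model does with the gap.** Group and group-by-time are in the model, so a different amount of missing data in each arm does not by itself violate missing-at-random. Under that assumption the model fills the gap with what patients who stayed, with the same earlier scores, would predict. Bias equals the drop-out share times the gap between that prediction and the true unseen score.

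**4. Illustration (my assumptions, not the documents' figures).** Compliant TFM patients change by 1.93 and waitlist patients by 0.94. A share q of the TFM arm meets the rule and ends at 0.94. Mean changes on days 10, 20 and 30 are 0.64, 1.29, 1.93 (TFM) and 0.31, 0.63, 0.94 (waitlist). Non-compliers follow TFM to day 10, then gain at the waitlist rate, reaching 0.64 + 0.32 = 0.96 on day 20. SD is 0.47 and within-patient correlation 0.6 at all visits. Age and baseline are left out.

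- All-randomized difference: 0.99 × (1 − q).
- Data stop after day 10: the day-10 scores look like everyone else's, so the model returns 0.99.
- Data stop after day 20: the regression slope of day 30 on each earlier visit is 0.6 / (1 + 0.6) = 0.375. The day-20 shortfall is 1.29 − 0.96 = 0.33. The model returns 0.99 − q × 0.375 × 0.33.

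| q | All randomized | Stop after day 10 | Overstated by | Stop after day 20 | Overstated by |
|---|---|---|---|---|---|
| 10% | 0.89 | 0.99 | 0.10 | 0.98 | 0.09 |
| 20% | 0.79 | 0.99 | 0.20 | 0.97 | 0.17 |
| 30% | 0.69 | 0.99 | 0.30 | 0.95 | 0.26 |

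If the unseen course matches that of compliers, the bias is 0. If scores are still collected and used, this bias does not arise.

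**The case against.** The other side has four good arguments.

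First, a reader might infer that section 2.2.4 flatly contradicts the intention-to-treat statement. The documents do not support that. Nothing says drop-outs' scores are deleted or excluded, and section 2.9 keeps every randomized patient with whatever data exist. That collection stops is an inference from the withdrawal wording and the 20% inflation. This stands, and it makes the point conditional.

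Second, a reader might infer that missing data that differ by arm are beyond the mixed model's repair. That is too strong. The model conditions on group and on the scores from days 10 and 20. Where poor early response drives non-attendance and those scores are seen, much of the bias goes.

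Third, a large inflation of false positives is tempting to claim. Removing the 20% of TFM patients with the least improvement shifts the mean by 0.350 × 0.47 = 0.164 points, against a standard error of √(0.3434/28) = 0.111. A zero-null test would reject about 11% of the time with a bias of 0.08, and about 30% with 0.16. But this describes a comparison of completers that ignores the earlier visits, which is not the planned analysis. With a removal score correlated 0.5 with every visit and a within-patient correlation of 0.6, the completers' bias of 0.08 falls to about 0.02 once days 10 and 20 are used, or to about 0.04 with day 10 alone. It also charges the whole all-cause dropout allowance to one rule in one arm.

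Fourth, criterion 5 covers both arms. If untreated waitlist patients seek other help more often, losing the most fatigued of them would flatter the waitlist mean and shrink the TFM effect. Net inflation is not established.

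What survives is that the protocol states a rule under which primary-outcome data can be lost. That goes beyond detail commonly left to an analysis plan.

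**Conclusion.** The concern holds in conditional form. Section 2.2.4 treats non-adherence, stopping treatment and outside fatigue treatment as leaving the trial, and the article does not reconcile this with an analysis of all randomized patients. If scores stop at that point, the day-30 comparison estimates an effect as if these patients had remained compliant. Missing-at-random is then a weak support: the event that ends observation is itself a change of treatment, and patients who stay on TFM are a doubtful guide to those who left it.

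The size is undetermined. The documents give no non-compliance rate, and the pilot had no dropouts. Under the stated assumptions the overstatement is about 0.1 to 0.3 PFS points for 10% to 30% of the TFM arm with data stopping after day 10, and about 0.09 to 0.26 after day 20. It is zero if the unseen scores follow the model's predictions. Against an assumed difference of 0.99 and a margin of 0.5, the upper values would matter. For criterion 5 the direction is uncertain.

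**What to change.** - Reword criteria 4 and 5, and the part of criterion 2 about stopping the prescribed treatment, as discontinuation of the intervention or protocol deviation, separate from withdrawal from the trial.
- State that the PFS on days 10, 20, 30 and 60 and the day-30 blood and fecal samples are still collected from these patients, and analysed in the randomized arm, unless consent is withdrawn.
- Use the threshold of 12 sessions only to define a supportive per-protocol analysis.
- Optionally, add a sensitivity analysis for departures from missing-at-random. Its form can be left to the analysis plan.

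The cost is protocol wording, a few retained visits that are already scheduled, and a somewhat diluted estimate, which is what an intention-to-treat effect should reflect. The sample size of 35 per arm does not change. The change should be made promptly, because missed assessments cannot be recovered. Whether a patient's treatment continues is a clinical matter and is not at issue here.
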